**Analysis**

1. For the first phase of the project, corresponding to the RSL, a statistical combination of the results will be carried out independently, both for the randomized clinical trials and for cohort studies, through a meta-analysis, following an exploration of the presence of heterogeneity through the inconsistency test (I2) and the p-value of the chi-square test, and if there is variation in the definition of the evaluated outcomes. The statistical combination of the results will be made through meta-analysis of fixed effects, or in the case of heterogeneous data, a random effects model will be used. A sensitivity analysis will be carried out to study the influence of the risk of bias in the results of the meta-analysis.
2. For the neuromarketing strategy, corresponding to the final phase of the study, descriptive analysis of the data will be carried out. The normality of the variables will be evaluated by the Shapiro-Wilk test. The difference between the averages of the variables of emotional reaction and attention will be carried out by means of an analysis of variance (ANOVA) for dependent samples in case the variables are distributed normally, otherwise this difference will be analyzed by means of a Kruskal-Wallis test. For the analysis, statistics will be used for paired studies, taking into account that the subjects are part of the evaluation of all interventions.
3. For the results of the survey, in which the recall of the contents of the capsules will be evaluated, a proportional difference will be made between the groups with a good level of recall and those with a low level of recall for each category of educational level. The analysis of the collected data will be made using the statistical software STATA 12.0®.

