Based on the results of the systematic review of strategies for the transfer and social appropriation of knowledge, on the results of formal consensus of experts, and on the theoretical foundations of neurocognition and neuromarketing, the design of health knowledge capsules will be developed together with experts in health psychology, promotion and prevention in health, as well as experts in diagramming and development of audiovisual products. During this phase the final scripts, the graphic outline of the clips, their duration, the soundtrack and the production will be created, based on the results of the previous phases.

1. **Phase 5. Evaluation of effectiveness of knowledge capsules in terms of social appropriation of knowledge.**

A neuromarketing strategy will be applied in the Cognitive Neuroscience and Communication Laboratory of the National University of Colombia, with the objective of evaluating the effectiveness of the knowledge capsules in maternal and neonatal health in terms of social appropriation of knowledge, using measurements of attention, emotional response and remembrance.

The analysis will be conducted to find differences between subgroups or categories of educational level, defined as follows:

0 = No study

1 = Primary or Baccalaureate (basic education or secondary education)

2 = Higher Education (undergraduate and postgraduate)

*- Design:* Cross-over experimental study in which a group of pregnant women, non-pregnant women and adult men will be exposed to 13 clips, 12 of which will be produced through this knowledge transfer strategy and one will be an unrelated standard video that will be used as a control. The order of viewing the videos will be assigned randomly for each subject, so that each subject will have 13 evaluations. The random allocation tables will be generated by computer, and one will be made for each educational stratum (without education, with primary or secondary education, and with post-secondary education) and group (pregnant woman, non-pregnant woman and man). It is expected to have a minimum sample of 150 subjects.

*- Population and sample:*

- Inclusion criteria:

Pregnant women, non-pregnant women and men over 18 years of age, who agree to participate in the study through informed consent.

- Exclusion criteria:

participants who presented serious health problems linked to pregnancy or who presented any clinically significant visual and auditory problems, which affected the viewing of the videos.

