*- Type of sampling:* not probabilistic, for convenience.

*- Sample size:*

Using the statistical analysis program for biomedical, social and behavioral sciences G * Power 3, the sample size was calculated for a one-way analysis of variance (ANOVA) design and fixed effects, using the F statistic. The selection of the parameters was made for the recall outcome, expecting that the differences of the capsules compared with the video control would be moderate. The parameters were therefore defined as follows: moderate effect size f = 0.3; power (1-β) = 0.90 and alpha (α) = 0.05 for three groups. The calculation yielded a result of 144 for the total sample. Considering that there would be no follow-up of the participants and the measurements would be taken in a single session, a low number of losses was estimated (mainly due to failures in the registry), so a minimum of 150 subjects was defined as a total sample, 50 for each group.

*Process:*

All participants will sign an informed consent (Annex 1) after explaining the objectives of the study and procedures that will be carried out. Participation will be completely voluntary.

The procedure consists of the projection of 12 health knowledge capsules of approximately 35 seconds each, and a control clip, not related to the subject. The control clip will be a standard video, which provides information on reproductive health and maternal safety, but which has not been designed based on evidence or following strategies based on neuromarketing.

The observation of the videos will be free; that is, they will not be explained to the participants during the screening, or the content of them. All the videos will be seen by the participants, but the observation of each one will be assigned in a random way.

The successive order of visualization of the videos is presented in Figure 1. It shows the successive ordering of the clips. However, the actual order of visualization of the clips will be done randomly for each of the subjects.

[figure not shown]

***Figure 1.*** *Form in which the assignment and evaluation of the effect of each intervention is planned.*

The process of consolidating results will be done for each clip as shown in Figure 2.

***Figure 2.*** *Selected sample, and methodological format of analysis of the clips*

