***Statistic analysis:***

Hypotheses raised:

- **Study hypothesis 1**

Comparison between capsules and video control

H0: μ capsule X = μ video control

Ha = μ capsule X ≠ μ video control

*μ = average attention, emotional reaction and recall*

- **Study hypothesis 2**

Comparison between groups: men, non-pregnant women, pregnant women

H0: μ1 = μ2 = μ3

Ha: ∃μj ≠ μ j = 1, 2, 3

*μ = average attention, emotional reaction and recall*

- **Study hypothesis 3**

Comparison between levels of schooling: none, primary, baccalaureate, undergraduate, postgraduate

H0: μ1 = μ2 = μ3

Ha: ∃μj ≠ μ j = 1, 2, 3, 4, 5

*μ = average attention, emotional reaction and recall*

- **Study hypothesis 4**

Comparison between family history: children, no children

H0: μ1 = μ2

Ha: μ1 ≠ μ2

*μ = average attention, emotional reaction and recall*

A descriptive analysis of the measured variables will be carried out. The qualitative variables will be described in proportions, and calculations for averages and standard deviation that follow a normal distribution will be performed for quantitative variables. For variables that do not follow this distribution, medians and interquartile ranges will be calculated. The normality of the variables will be evaluated by the Shapiro-Wilk test.

The difference between the averages of the variables of emotional reaction and attention will be carried out by means of an analysis of variance (ANOVA) for dependent samples, taking into account the effect of drag. For these comparisons, the non-parametric tests of Kruskal Wallis and the Wilcoxon rank sum will be used, according to the number of levels of each factor.

For the results of the survey, in which the recall of the contents of the capsules will be evaluated after their screening, an analysis will be made to compare the difference in proportions between the groups with a good level of recall and those with a low level of recall for each category of educational level.

Statistical software Stata 13.1 will be used to analyze the data.

1. **Phase 6. Final production of the health capsules in maternal and neonatal safety**

Professional experts in the layout and development of audiovisual animation products will carry out the final production process, taking into account the changes suggested by the analysis of results of the neuromarketing strategy.

- - - 1. **Ethical considerations**

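### For attention and emotional reaction, the ANOVA's default common error may not fit the capsule-versus-control contrasts; use each contrast's own paired error

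*Protocol*

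**What the plan says.** Phase 5 shows every participant 13 clips in random order. They "will be exposed to 13 clips, 12 of which will be produced through this knowledge transfer strategy and one will be an unrelated standard video". The Process paragraph describes "12 health knowledge capsules of approximately 35 seconds each, and a control clip, not related to the subject" and adds that the control "has not been designed based on evidence or following strategies based on neuromarketing".

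Hypothesis 1 in the statistical analysis is a set of single two-sided contrasts, one per capsule: "Ha = μ capsule X ≠ μ video control". For attention and emotional reaction, the comparison is made "by means of an analysis of variance (ANOVA) for dependent samples, taking into account the effect of drag". The next sentence adds rank tests: "For these comparisons, the non-parametric tests of Kruskal Wallis and the Wilcoxon rank sum will be used". Recall is handled separately, by comparing proportions.

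The Analysis part of the executive summary, item 2, says that "statistics will be used for paired studies, taking into account that the subjects are part of the evaluation of all interventions".

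Neither place says which error term the individual capsule-versus-control contrasts use, or how unequal difference variances are handled.

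**The concern.** A classical ANOVA for dependent samples has one residual term, the subject-by-clip mean square, and uses it for every contrast between clips. For a single contrast this is right only if the variance of that difference equals the average over all clip pairs.

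Here that average is mostly about something else. Among 13 clips there are 13 × 12 / 2 = 78 pairs. Of these, 12 × 11 / 2 = 66 are capsule-capsule and 12 are capsule-control. The capsules come from one production process and have similar length, and the control was made another way. A participant's responses to two capsules may well agree more closely than the responses to a capsule and the control. Random viewing order balances position effects but does not change this structure.

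Hypothesis 1 is the effectiveness comparison and uses only the 12 minority pairs. If their difference variance is above the average, the tests reject too often and any interval reported is too narrow. This applies to each single contrast, before any question of multiplicity.

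**Working it through.** **The plan's own figure.** The sample size section uses a one-way ANOVA with three groups, f = 0.3, α = 0.05 and power 0.90. The noncentrality is 0.3² × 144 = 12.96 with 2 and 141 degrees of freedom, which gives power 0.9008, so 144 reproduces. The figure concerns three between-subject groups and does not depend on the error term discussed here.

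**Inputs.** From the protocol: 12 capsules, one control and 150 participants. Assumed, because the protocol gives none: capsule SD 1, control SD s, correlation r_cc between two capsules and r_c0 between a capsule and the control.

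**Formulas.**
- Variance of a capsule-capsule difference: V = 2(1 − r_cc).
- Variance of a capsule-control difference: T = 1 + s² − 2·s·r_c0.
- Twice the pooled mean square is the average over all pairs: (66V + 12T)/78.
- Pooled SE divided by true SE: √[(66·V/T + 12)/78].
- Actual two-sided error at nominal 5%: 2[1 − Φ(1.96 × ratio)].

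The ratio is below 1 exactly when T exceeds V.

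| r_cc | r_c0 | s | V | T | SE ratio | Actual error |
|---|---|---|---|---|---|---|
| 0.5 | 0.5 | 1 | 1.00 | 1.00 | 1.000 | 5.0% |
| 0.7 | 0.6 | 1 | 0.60 | 0.80 | 0.888 | 8.2% |
| 0.7 | 0.5 | 1 | 0.60 | 1.00 | 0.813 | 11.1% |
| 0.7 | 0.4 | 1 | 0.60 | 1.20 | 0.760 | 13.7% |
| 0.6 | 0.5 | 0.7 | 0.80 | 0.79 | 1.005 | 4.9% |
| 0.6 | 0.6 | 0.7 | 0.80 | 0.65 | 1.093 | 3.2% |
| 0.6 | 0.6 | 1.3 | 0.80 | 1.13 | 0.868 | 8.9% |

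Example, third row: (66 × 0.60/1.00 + 12)/78 = 51.6/78 = 0.6615, and its square root is 0.813.

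**When the direction can reverse.** For a given r_c0, T is smallest at s = r_c0, where it equals 1 − r_c0². The pooled SE can therefore reach or exceed the true one only if r_c0² ≥ 2·r_cc − 1. With r_cc = 0.7 this needs r_c0² ≥ 0.40. The three assumed values give 0.36, 0.25 and 0.16, so no control SD removes the bias there; the best ratios are 0.973, 0.911 and 0.871. With r_cc = 0.6 it needs only r_c0² ≥ 0.20, which 0.5 and 0.6 both satisfy.

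**Simulation.** With n = 150 and 4,000 data sets per scenario (Monte Carlo SE about 0.0034), the pooled test at correlations 0.7 and 0.4 rejected in 13.3%. The test on per-subject differences rejected in 4.1% to 5.9% across the scenarios tried. That spread is somewhat wide for its Monte Carlo error. A rerun with 40,000 data sets (Monte Carlo SE √(0.05 × 0.95/40,000) = 0.0011) put the paired test at 4.8% to 4.9%.

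**Omnibus test.** The Greenhouse-Geisser epsilon for the three rows with r_cc = 0.7 is 0.97, 0.91 and 0.84. The correction adjusts only the overall F and leaves the contrast standard errors as they are.

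**The case against.** **The protocol never says that a pooled error is used.** An ANOVA for dependent samples with two levels, one capsule and the control, is the paired t-test and already uses that difference's own SD. The summary's promise of paired statistics is consistent with this. The point stands as a caution: the pooled error is the named method's default, not stated text, and a statistical analysis plan could settle it. But a carry-over term, and subjects described as evaluated on all interventions, fit one 13-clip model better than twelve separate two-clip analyses.

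**The direction is not established.** A reader might infer that the planned standard errors are too small and the false-positive rate above 5%. The documents do not support that. They give no correlation or SD, and a less variable control can cancel the bias or turn it round, as the fifth and sixth rows of the table show. This part of the objection stands in full.

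**The control may be less of an outsider than it looks.** Its length and producer are not given, and although it is called unrelated, the Process paragraph also says that it covers reproductive health and maternal safety. The capsules themselves differ by phase and mode of delivery. Greater similarity among the capsules is therefore plausible, not documented.

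**Other tests are named for the same comparisons.** The rank-sum test ignores the pairing. With positive within-subject correlation it is conservative (simulated error 0.3% to 2.7%). That is a separate weakness and does not repair the ANOVA.

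**Recall is outside the point.** It drove the sample size but is analysed by proportions.

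**Conclusion.** The point holds conditionally. For attention and emotional reaction, the named ANOVA read as one 13-clip model rests the capsule-versus-control tests on an error averaged mainly over other pairs, and the design gives reason to doubt that this average fits them.

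With similar SDs and a control that correlates less with the capsules than they do with each other, the standard errors are too small: ratio 0.89 to 0.76 and per-contrast error 8% to 14%, assuming correlations of 0.7 and 0.6 to 0.4. With equal correlations and SDs there is no bias. With a less variable control, the standard errors can be right or too large. None of these inputs is in the protocol, so it cannot be said that the planned tests are anti-conservative. What can be said is that their validity depends on an unverified assumption that the analysis does not need. The sample size of 144, raised to 150, is not affected.

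**What to change.** For hypothesis 1 on attention and emotional reaction, state that each capsule is tested with the per-subject difference, capsule X minus control, using that difference's own SD for the test and for any interval. If the carry-over term is to be kept, use instead a mixed model whose covariance gives the control its own variance and its own correlation with the capsules. Do not use the ANOVA's common mean square for these contrasts. Apply the Greenhouse-Geisser correction only to any 13-clip omnibus F test that is kept.

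The cost is analysis wording, with the same data. Error degrees of freedom fall from 149 × 12 = 1,788 to 149, which matters little. Where the pooled error was too small, intervals widen by the inverse of the ratio: 1/0.888 = 1.13 to 1/0.760 = 1.32, or about 13% to 32% in the three scenarios with capsule-capsule correlation 0.7. Where it was too large they narrow, for example 1/1.093 = 0.91.

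### For capsule versus control clip on attention and emotional reaction, the non-parametric tests named are for independent samples, although every subject views all 13 clips

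*Protocol*

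**What the plan says.** The design is within-subject for the clips. In Phase 5 (Design) the protocol states: "The order of viewing the videos will be assigned randomly for each subject, so that each subject will have 13 evaluations". Hypothesis 1 in the Phase 5 statistical analysis is headed "Comparison between capsules and video control".

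For attention and emotional reaction, the same section plans an "analysis of variance (ANOVA) for dependent samples, taking into account the effect of drag". It then states that for these same comparisons "the non-parametric tests of Kruskal Wallis and the Wilcoxon rank sum will be used, according to the number of levels of each factor".

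The Executive summary (Analysis, item 2) gives the same parametric plan and, if normality fails, says "otherwise this difference will be analyzed by means of a Kruskal-Wallis test". Its next sentence promises that "statistics will be used for paired studies, taking into account that the subjects are part of the evaluation of all interventions".

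Recall is handled separately, by a comparison of proportions.

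**The concern.** Kruskal-Wallis and the Wilcoxon rank sum take their null distributions from independent groups. Phase 5 chooses between them by how many levels a factor has, not by whether the factor varies within or between people. Applied to clips, the rule gives Kruskal-Wallis for 13 clips and the rank sum for one capsule against control, and both treat 13 measurements on one person as coming from 13 people. The person-to-person variation that the crossover was meant to remove stays in the comparison.

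Hypothesis 1 is the effectiveness question, and Phase 6 revises the capsules according to these results. A capsule that does differ from the control on attention or emotional reaction could be reported as no different. The Executive summary also contradicts itself in consecutive sentences, so an analyst cannot follow both.

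**Working it through.** **1. The plan's own figure.** Sample size section: one-way fixed-effects ANOVA, three groups, f = 0.3, alpha 0.05, power 0.90. With λ = N·f² = 144 × 0.09 = 12.96 on 2 and 141 degrees of freedom, power is 0.9008, so N = 144 is reproduced. At N = 150, λ = 13.5 and power is 0.913. This calculation is for independent groups and does not bear on the clip comparison.

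**2. Which hypotheses are paired.** Hypothesis 1 (capsule versus control) compares values from the same people. Hypotheses 2 (participant group), 3 (schooling) and 4 (children or none) compare different people.

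**3. True size for clip comparisons.** Inputs: 150 subjects and 13 clips (protocol); within-subject correlation ρ = 0.3, 0.5, 0.7, exchangeable across clips (assumed). With correlation ρs between ranks, the variance of a rank difference between two clips is (1 − ρs) times what the independent-sample test assumes. For normal data, or any monotone transform of them, ρs = (6/π)·arcsin(ρ/2). Hence, approximately:

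- rank sum: size = 2·[1 − Φ(1.96/√(1 − ρs))]
- Kruskal-Wallis, 13 clips: size = P(χ² on 12 df > 21.03/(1 − ρs))

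| ρ | ρs | Rank sum, formula | Kruskal-Wallis, formula |
|---|---|---|---|
| 0.3 | 0.288 | z = 2.32, 2.0% | cut-off 29.5, 0.33% |
| 0.5 | 0.483 | z = 2.72, 0.6% | cut-off 40.6, 0.006% |
| 0.7 | 0.683 | z = 3.48, 0.05% | cut-off 66.3, below 0.001% |

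Simulation with skewed (log-normal) data, 2,500 replicates per setting, agrees and shows that the matched tests hold their level:

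| ρ | Rank sum | Signed rank | Kruskal-Wallis | Friedman |
|---|---|---|---|---|
| 0.3 | 2.1% | 5.2% | 0.3% | 5.2% |
| 0.5 | 0.5% | 4.8% | 0% | 4.4% |
| 0.7 | 0.04% | 4.3% | 0% | 4.6% |

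At ρ = 0 all four lie between 4.3% and 4.8%, so the dependence is the cause.

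**4. Power, one capsule versus control** (normal data, 150 subjects; ρ = 0.3 / 0.5 / 0.7; 4,000 replicates at 0.3 SD, 1,000 at the others):

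| Difference | Rank sum | Signed rank |
|---|---|---|
| 0.2 SD | 40 / 36 / 32% | 54 / 67 / 87% |
| 0.3 SD | 75 / 78 / 86% | 85 / 94 / 99.5% |
| 0.5 SD | 99.8 / 100 / 100% | 99.9 / 100 / 100% |

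Across all 13 clips with the control 0.2 SD below every capsule, Kruskal-Wallis has 10 / 2 / 0% and Friedman 35 / 50 / 76%. At 0.5 SD Kruskal-Wallis has 98 / 99 / 99% and Friedman 100%. Separate runs differ only by simulation error (at 0.3 SD, for example, 75 / 81 / 85% against 85 / 95 / 99%).

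**5. Hypotheses 2 to 4, one value per subject.** Size of the named tests at the same correlations: Kruskal-Wallis for three groups, 4.7 / 5.0 / 4.6% per clip and 5.1 / 4.7 / 4.4% on subject means; rank sum for two groups per clip, 5.8 / 4.8 / 4.6%. These are close to 5%, so nothing needs changing there.

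**The case against.** The strongest defence is that the sentence was written with the between-person factors in mind. Those have 3, 5 and 2 levels, which suits a rule based on the number of levels, and the tests are appropriate there. That stands for hypotheses 2 to 4. It does not rescue hypothesis 1: the sentence refers back to the dependent-samples ANOVA, and the Executive summary makes Kruskal-Wallis the substitute for that ANOVA.

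The defence also limits the consequence. The error is conservative and creates no false positives. The protocol expects moderate differences from control, f = 0.3, which for two equal groups is d = 2f = 0.6 SD, and at that size little power is lost. But f was set for recall, not for the two outcomes concerned. The study is also called a pilot. These points reduce the weight of the finding, but the named test remains wrong for these data.

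A reader might go further in four ways that the documents do not support:

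- **That every comparison is invalid.** Hypotheses 2 to 4 are sound with one value per subject.
- **That false positives are inflated by stacking 150 × 13 = 1,950 rows as independent.** No section plans this, and the Process section consolidates results clip by clip.
- **That the non-parametric branch is the likely one, or replaces the ANOVA outright.** No distribution is given for either outcome. The Phase 5 sentence states no condition, but the Executive summary does, and Phase 5 introduces the Shapiro-Wilk test just before.
- **That losing the carry-over (drag) term is peculiar to the named tests.** Friedman and signed rank cannot carry it either. Viewing order is randomised and a washout sequence is planned.

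**Conclusion.** The point holds for hypothesis 1 on attention and emotional reaction, whenever the non-parametric branch is used. The protocol names independent-sample tests for paired data in two places and contradicts its own paired-statistics statement. This is a wrong rule as written, not a detail left to an analysis plan.

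The direction, p-values too large, holds for any positive within-subject correlation. The size depends on that correlation, which the documents do not give. Over 0.3 to 0.7, a nominal 5% test runs at about 2% or less (rank sum) and 0.3% or less (Kruskal-Wallis). The power loss for a single capsule is about 10 to 18 percentage points at 0.3 SD, larger at 0.2 SD and negligible from 0.5 SD upwards. Recall and hypotheses 2 to 4 are outside the finding.

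**What to change.** Amend the non-parametric sentence in both places (Executive summary, Analysis item 2; Phase 5 statistical analysis) so that they agree:

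- When normality fails, compare clips with the Friedman test, and each capsule with the control clip by the Wilcoxon signed rank test.
- Use Kruskal-Wallis or the Wilcoxon rank sum only for hypotheses 2 to 4, on one value per subject, either per clip or averaged over clips.

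State the normality condition in Phase 5 as well. If the carry-over term is to be kept in this branch, a mixed model with clip and viewing position as fixed effects and subject as a random effect is an option; the rank tests cannot include it.

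The cost is two sentences of protocol text. No additional data, subjects or procedures are needed.

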During the screening of the health knowledge capsules, the eye tracking method will be applied to evaluate the attention of the subjects before the visual stimulus of the health capsules. By means of a Tobii TX 300 eye tracker and the Tobii Studio Software, the pupillary size in arbitrary units (AU), and the duration and direction of the fixation in seconds will be measured. Areas of interest will also be recorded, according to the stimuli in which the attention is fixed, the duration, and the order in which the visual exploration is performed.

The monitoring of the autonomous activity will be carried out through the registration of the electrodermal activity (Galvical Skin Reaction), which allows the evaluation the state or emotional reaction of the subjects. The record of electrodermal activity will be measured by the computerized psychophysiological recording equipment I-330-C2 + 12. (J & J Enterprises Seattle, WA). The measuring electrodes will be placed on the distal phalanx of the third and fourth finger of the non-dominant hand with SE-35 sensors connected to a T-601 preamplifier (J & J Enterprises Seattle, WA). For the analysis of results, the USE3 Software from Physiolab will be used (J & J Engineering, 2004).

The analysis of skin conductance data will be carried out with a procedure performed by Benedek and Kaernbach, through which the amplitude of the electrodermal response to a stimulus is obtained. Thus, two register values ​​will be recorded to calculate the amplitude: the conductance recorded in the lowest time of the latency period and the conductance peak. Subsequently, these values ​​and their registration will be subtracted. This analysis will be performed for each event identified in each capsule by each subject, to obtain an average of the conductance amplitudes for each grouping of images-events (positive, negative and neutral).

Between each video there will be a break of 5 to 10 seconds, and before starting the next video for evaluation there will be a neutral sequence in order to calibrate the response of the individual to a neutral state: this is considered to be the washout period between each video.

A parametrization of the measurements will be carried out in order to be able to relate both variables. Subsequently, a survey will be applied to evaluate the recall component.

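### Recall set the sample size and appears as a mean in all four hypotheses, but its only stated analysis is a good/low comparison by educational level, so hypotheses 1, 2 and 4 have no recall test and the 90% power does not describe the recall analysis

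*Protocol*

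**What the plan says.** **Sample size (Protocol, Phase 5, Sample size).** "The selection of the parameters was made for the recall outcome", with the rationale "expecting that the differences of the capsules compared with the video control would be moderate". The method is "the sample size was calculated for a one-way analysis of variance (ANOVA) design and fixed effects, using the F statistic", with "moderate effect size f = 0.3" and "power (1-β) = 0.90 and alpha (α) = 0.05 for three groups". The result is 144, raised to 150, or 50 per group.

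**Hypotheses (Protocol, Phase 5, Statistic analysis).** Hypothesis 1 compares each capsule with the control video. Hypothesis 2 compares men, non-pregnant women and pregnant women. Hypothesis 3 compares levels of schooling, and hypothesis 4 compares people with and without children. Each defines its parameter as "average attention, emotional reaction and recall".

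**Analysis (same section).** The dependent-samples ANOVA, with an allowance for carry-over, is assigned to emotional reaction and attention. The Kruskal-Wallis and Wilcoxon tests are given for those same comparisons. Recall has its own paragraph, which says the analysis will "compare the difference in proportions between the groups with a good level of recall and those with a low level of recall" within or across educational categories. Item 3 of the Analysis part of the Executive summary gives recall the same treatment. No cut-off for good recall is stated.

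**Measurement (Phase 5, Process).** After the description of the eye-tracking and skin-conductance recordings, the text adds: "Subsequently, a survey will be applied to evaluate the recall component".

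**The concern.** Recall is one of three measures of effectiveness in the specific objectives, and it is the one that fixed the number of participants. The sizing, the hypotheses and the analysis should therefore describe the same comparison on the same scale. They do not. The sizing is for a mean in three independent groups, justified by a capsule-control difference. The hypotheses are on a mean and cover four factors. The analysis is on a binary outcome and covers one factor, education.

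If the plan is followed literally, the report could not say whether any capsule is recalled better than the control clip, or whether pregnant women recall differently from the other two groups. Readers would also credit the recall result with 90% power that was calculated for something else. With no cut-off fixed, the good/low result also depends on a threshold that could be chosen after the data are seen.

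**Working it through.** **1. Which recall comparisons are stated as hypotheses, and which are analysed**

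| Hypothesis | Comparison | Stated for mean recall? | Recall analysis given? |
|---|---|---|---|
| 1 | capsule vs control | yes | none |
| 2 | men, non-pregnant, pregnant women | yes | none |
| 3 | schooling | yes | good/low proportions only |
| 4 | children, no children | yes | none |

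Attention and emotional reaction have a named test throughout. Recall has one only for hypothesis 3, and there on a different scale from the stated mean.

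**2. Reproducing the protocol's figure**

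Inputs from Phase 5, Sample size: k = 3 groups, f = 0.3, α = 0.05, power 0.90. Power is the probability that a noncentral F with (k − 1, N − k) degrees of freedom and noncentrality λ = N·f² exceeds the 5% critical value.

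- N = 144: λ = 144 × 0.09 = 12.96, df (2, 141), power 0.901. This is the smallest N reaching 0.90.
- N = 150: λ = 150 × 0.09 = 13.5, df (2, 147), power 0.913.

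The stated 144 is correct for its inputs. It describes a comparison of mean recall between three independent groups, which is hypothesis 2.

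**3. The same effect after a good/low split (illustration)**

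The protocol gives no cut-off and no distribution for recall. Assume a normal score with standard deviation 1, three groups of 50, and group means giving f = 0.3 in one of two patterns: equally spaced (−0.367, 0, 0.367) or one group different (0.424, −0.212, −0.212). Split at a common cut and test the three proportions p_j by a 2-df chi-square, with noncentrality

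λ = N × mean[(p_j − p̄)²] / [p̄(1 − p̄)].

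- 50/50 cut, equally spaced: p = 0.357, 0.500, 0.643. The mean squared deviation is 2 × 0.143² / 3 = 0.01363, so λ = 150 × 0.01363 / 0.25 = 8.18 and power is 0.73. The one-group pattern also gives 0.73.
- 30% good, equally spaced: p = 0.180, 0.292, 0.428. λ = 150 × 0.01028 / 0.21 = 7.34, power 0.68. By symmetry, 70% good gives the same.
- 30% good, one group different: p = 0.452, 0.224, 0.224, power 0.73.
- 70% good, one group different: p = 0.835, 0.632, 0.632. λ = 150 × 0.00916 / 0.21 = 6.54, power 0.62.

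| Overall good/low split | Power at N = 150 |
|---|---|
| score not split (ANOVA) | 0.91 |
| 50/50 | 0.73 |
| 30/70 or 70/30 | 0.62 to 0.73 |
| 20/80 or 80/20 | 0.51 to 0.67 |
| 10/90 or 90/10 | 0.33 to 0.53 |

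Regaining 0.90 at a 50/50 split would take about 231 to 234 participants.

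**4. Capsule vs control**

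Every participant sees all 13 clips, so this contrast is within subject, while the calculation is for independent groups. The 90% therefore does not transfer to it in either direction. With 150 participants, one paired comparison at α = 0.05 and a standardised difference of 0.3 has power 0.73 if the two scores are uncorrelated and 0.95 at correlation 0.5. At α = 0.05/12 for twelve capsules these become 0.38 and 0.78. If f = 0.3 is read as a two-condition effect (difference 2 × 0.3 = 0.6), all four exceed 0.98. The protocol fixes neither the correlation nor the difference.

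**The case against.** The strongest reply is that the hypotheses do name recall against the control and across groups, so the intention is clear and only the wording of one paragraph is narrow. That supports the remedy but does not remove the conflict. A recall analysis is stated, twice, and it uses another scale and another factor. This is a contradiction within the protocol, not a detail left for a statistical analysis plan.

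Other parts of the reply stand, and they limit the point. A reader might infer each of the following, but the protocol does not support it:

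- **The control clip has no recall score.** The only basis is that the survey is described as covering the capsules' contents. Against it, each participant is to have 13 evaluations, the sizing refers to capsule-control differences in recall, and hypothesis 1 names recall. The survey itself is not shown. Control scoring is unclear, not absent.
- **Recall is asked once at the end and distorted by viewing order.** The text says the survey follows the screening, but not that it is given once. Order is randomised for each participant, so position effects balance across clips in expectation.
- **The recall groups are defined by the outcome.** This is probably translated wording for comparing the proportion with good recall across education levels.
- **The recall comparison would have under 30% power because it is made within education categories.** That needs an assumed even split of about 50 people per category. Most of the fall comes from the smaller subset: the unsplit ANOVA at 50 people has λ = 50 × 0.09 = 4.5 and only 44% power.
- **The study cannot assess effectiveness at all.** Attention and emotional response keep a planned capsule-control comparison, and the study is described as a pilot.

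**Conclusion.** The point holds. The only analysis stated for recall is a good/low comparison by educational category. It leaves hypotheses 1, 2 and 4 without a recall test and addresses hypothesis 3 only on a binary scale. The 90% power is correctly calculated, but for a three-group comparison of mean recall that the analysis text does not contain.

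The conflict is read directly from the text and needs no assumption. The size of the power loss does: 91% against about 73% at an even cut, or 62% to 73% at 30/70 or 70/30, rests on a normal score, equal groups, f = 0.3 and assumed cut-points, and is illustrative. These figures concern a three-group comparison and say nothing about capsule vs control. It would go too far to conclude that the study is underpowered for that contrast, because the protocol lacks the inputs needed to judge it.

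**What to change.** 1. Replace the recall paragraph in Phase 5, and the matching item in the Executive summary. Analyse recall as a per-clip score (proportion of items correct) in a repeated-measures model with clip and viewing position as fixed effects and subject as a random effect for hypothesis 1. Add terms for participant group, education and children for hypotheses 2 to 4.
2. Keep the good/low percentages as a descriptive or secondary summary.
3. Before data collection, confirm that the survey scores the control clip with items comparable in number and difficulty to those for the capsules. Control recall that is not collected cannot be recovered later.
4. State in the sample-size text that the 90% power applies to the three-group comparison of mean recall (hypothesis 2), and not to capsule vs control or to the good/low split.

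The cost is slightly more survey and analysis work, with no added participants or sessions. One limitation remains. Items on different content cannot be made exactly equal in difficulty, so part of any capsule-control difference in recall may reflect the questions, and the report must say so.
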